| Objectives, Specific Aims and Rationale Overall Primary Objective:  1a) To investigate the risk of worsening of renal function using eGFR (using CKD EPI formula) in relation to bilirubin levels in type2 diabetic patients, in a real-world setting.  1b) To investigate the risk of worsening of renal function using eGFR in relation to bilirubin levels in hypertensive patients, in a real-world setting.  Secondary objectives:  2a) To investigate the risk of worsening of renal function using urine albumin creatinine ratio (UACR) in relation to bilirubin levels in type2 diabetic patients, in a real-world setting.  2b) To investigate the risk of worsening of renal function using UACR in relation to bilirubin levels in hypertensive patients, in a real-world setting.  Exploratory objectives:  3a) To investigate the risk of worsening of renal function using amount of protein in urine in relation to bilirubin levels in type2 diabetic patients, in a real-world setting.  3b) To investigate the risk of worsening of renal function using amount of protein in urine in relation to bilirubin levels in hypertensive patients, in a real-world setting.  Specific aims:   \| **Primary objectives**  1a) To investigate the risk of worsening of renal function using eGFR in relation to bilirubin levels in type2 diabetic patients, in a real-world setting.  1b) To investigate the risk of worsening of renal function using eGFR in relation to bilirubin levels in hypertensive patients, in a real-world setting. \| **Outcome measure**  Time to first of first two consecutive measurements of eGFR that are 30 percent less than the eGFR at baseline. \| **Hypothesis tested**  1a) Naturally elevated serum bilirubin level of type2 diabetic patients is associated with slower degradation of the renal function when renal function is measured using eGFR.  1b) Naturally elevated serum bilirubin level of hypertensive patients is associated with slower degradation of the renal function when renal function is measured using eGFR. \| \| --- \| --- \| --- \| \| **Secondary objective**  2a) To investigate the risk of worsening of renal function using urine UACR in relation to bilirubin levels in type2 diabetic patients, in a real-world setting.  2b) To investigate the risk of worsening of renal function using UACR in relation to bilirubin levels in hypertensive patients, in a real-world setting. \| **Outcome measure**  Time to first observation of albuminuria (UACR >30mg/g) during the follow up period. \| **Hypothesis tested**  2a) Naturally elevated serum bilirubin level of type2 diabetic patients is associated with slower degradation of the renal function when renal function evaluated by UACR.  2b) Naturally elevated serum bilirubin level of hypertensive patients is associated with slower degradation of the renal function when renal function evaluated by UACR. \| \| **Exploratory objective**  3a) To investigate the risk of worsening of renal function using amount of protein in urine in relation to bilirubin levels in type2 diabetic patients, in a real-world setting.  3b) To investigate the risk of worsening of renal function using amount of protein in urine in relation to bilirubin levels in hypertensive patients, in a real-world setting. \| **Outcome measure**  Time to first observation of proteinuria during the follow up period. \| **Hypothesis tested**  3a) Naturally elevated serum bilirubin level of type2 diabetic patients is associated with slower degradation of the renal function when renal function evaluated by proteinuria.  3b) Naturally elevated serum bilirubin level of hypertensive patients is associated with slower degradation of the renal function when renal function evaluated by proteinuria. \|   **Rational:**  Recent investigations as well as meta-analyses indicate a strong association between serum bilirubin concentrations and renal outcomes. This association has led us to hypothesis that elevated bilirubin level is associated with slower degradation of kidney function. There are still discussions on this association because the previous investigations lack diversity in the patient population and did not adjust for the key confounders. We wish to conduct a retrospective study in a real-world setting to support or dispute this hypothesis. This study will provide the medical community extra piece of evidence for or against the bilirubin as a potential predictive marker for CKD progression as well as the target for preventative treatment option. |

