| Study Background Bilirubin is the most powerful endogenous lipophilic anti-oxidant and is eliminated through glucuronidation by uridine diphosphate glucuronosyltransferase 1 family, polypeptide A1 (UGT1A1). It has been hypothesized that naturally elevated level of bilirubin has a protective effect against renal outcomes. The mechanism of action is proposed to be anti-oxidative, with effects on inflammation, endothelial function, dyslipidaemia, and platelet hyperactivity (1,2). Recent investigations indicate strong associations between naturally elevated bilirubin concentrations and positive renal outcome in diabetic and or hypertensive patients (3,4,5,6).  Most of the currently available studies (3,5,6) were conducted in Asia. It is therefore unclear if the results would be similar in non-Asian populations. Wagner et al. (7) showed that the natural bilirubin level is usually higher in Asians than Europeans, hence it is plausible that the findings based on Asian population (in 3,5,6) may not extend to the European population. To best of our knowledge, Riphagen et al. conducted the only study outside of Asia, showing a positive effect of bilirubin on a composite endpoint consisting of serum creatinine doubling or end stage renal disease (4).  All of these studies consisted of approximately 5000 subjects or less and may not have been able to account for critical confounders such as hemoglobin or smoking status which we hope to capture through a real-world study.  Prior studies focused on two patient populations at risk of CKD, diabetics or hypertensive patients. However, because different studies used different endpoints and slightly different methodologies, it is difficult to make direct comparisons on the potential effect of bilirubin in the two populations. Thus, by creating two cohorts, diabetic cohort and the hypertensive cohort from the same database and applying the identical analysis method we may be able to make direct comparisons on the effect of bilirubin on CKD in these two populations. |
| Study Type Observational study, part descriptive and part analytical. |
| Study Design This will be a retrospective open cohort study.  The first cohort (CH1) will be the population with a diagnosis date of type 2 diabetes. The second cohort (CH2) will be the population with a diagnosis date of essential hypertension. |

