| Definition of the Study population This study will examine two patient cohorts who are at risk of CKD, diabetic and hypertensive patients. Eligible patients must have information recorded at least 12 months prior to the study index date and have up to standard (UTS). The study population will include patient records from January 2005 to January 2019.  **Inclusion criteria**  Cohort 1 (CH1) will include type 2 diabetes mellitus (T2D) patients along with any one of the following criteria (see Appendix 1 for the inclusion exclusion flow chart):   - Newly diagnosed T2D (MEDCODE 758 : Type 2 diabetes mellitus) - 2 prescriptions of diabetic medication (See Appendix 3 for the list of all drugs) - Hemoglobin A1c (HbA1c) value greater than 6.5   Cohort 2 (CH2) will include essential hypertension (EHT) patients along with the following criteria (see Appendix 2 for the inclusion exclusion flow chart):   - Newly diagnosed essential hypertension (see Appendix 4 for list of Read codes)   Time related variable including the index date and the follow-up is described in the following figure:  **Rolling index date**  (The date first diagnosed with DM2 or HT**)**  Pre-index period  1 years  Acute disease period  2 years  Follow up period  (Median follow up 5 years, minimum follow up 1 year)  **End of follow up**  (Either the date patient has transferred out from the practice  Or the last date of the record in the dataset)  **CH1**: no DM2 diagnosis nor related medication during this period **CH2**: no HT diagnosis nor DM2 diagnosis nor related medication during this period  Baseline is characterized based on the observation in these periods  January 2005  January 2019  **Exclusion criteria**  We will exclude the following patients based on the Read code during acute disease period (2 years after the rolling index date):   - Liver dysfunction including drug induced liver injury (diagnosis with Read code listed in Appendix 5 and/or Aspartate transaminase (AST) and alanine transaminase (ALT) levels outside of the normal range (AST: 8-48U/L, ALT: 7-55U/L) - Anemia (hemoglobin level below cutoff, female:120 male:130 g/L, or with the clinical annotation of primary or secondary anemia with the Read code listed in Appendix 6) - Human immunodeficiency virus (HIV) infection and or on HIV related medications (see Appendix 7). - All malignancies and or on medications related to the treatment for the malignancies (see Appendix 8). - Age < 40 (to exclude type 1 diabetic patients). - Any user of UGT1a1 inhibitors (see Appendix 9) during the acute disease period. - < 1 year of clinical records in the database before the index date - Pregnant women - Patients with clinical record of alcohol dependencies. - Any patients with less than two bilirubin measurements during the acute disease period.   **Objective-specific exclusion criteria**  For each endpoint, we impose the following additional exclusion criterion:   - For objectives 1a) and 1b) with the endpoint “First two consecutive measurements of eGFR that are 30 percent less than the last eGFR record during the acute disease period”, we will exclude patients without eGFR records during the acute disease period (2 years after the rolling index date). - For objectives 2a) and 2b) with the endpoint “First observation of albuminuria (UACR >30mg/g) during the follow up period.”, we will exclude patients with recorded UACR more than 30mg/g during the acute disease period. - For objectives 3a) and 3b) with the endpoint “First observation of proteinuria during the follow up period, we will exclude the patients with the recorded proteinuria (protein dipstick test result +, ++, or +++) during the acute disease period. |

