| Selection of comparison group(s) or controls We will stratify the patients based on the population median of the patient mean baseline serum bilirubin levels from the tests table under ENTTYPE 158. We consider the patients with less than or equal to the median serum bilirubin level to be the control group, and patients with greater than the median serum bilirubin level to be the exposure group.  The serum bilirubin levels are determined by the average of all the available measurements during the acute disease period (2 years after the rolling index date). We require at least two bilirubin measurements to be used to obtain an average estimate (this will account for the variability of bilirubin measurements). |
| Exposures, Outcomes and Covariates **Outcome:**  Outcomes will include the following events:  Primary objective: eGFR decline  1) First two consecutive measurements of eGFR that are 30 percent less than the last eGFR record during the acute disease period.  eGFR will be calculated using CKD EPI formula based on the recorded serum creatinine measurements in tests table ENTTYPE 165.  Secondary objective: Proteinuria  2) First observation of the proteinuria  Proteinuria is defined as the protein dipstick test results either +, ++ or +++, recorded in the tests table under ENTTYPE 431.  Exploratory objective: Albuminuria  3) First observation of the albuminuria  Albuminuria is defined as the recorded UACR measure in test table under ENTTYPE 469 greater than 30mg/g.  **Covariates:**  We will use all the available covariates (see Appendix 10) to calculate the propensity score that we will use for the inverse probability weighting of the Cox proportional hazard model.  We will include all the available covariates (see Appendix 10) in the baseline table.  We will include the following selected covariates in the multivariate Cox proportional hazard model:   - Age, Sex, Weight, BMI, Baseline eGFR, Baseline UACR, Baseline protein dipstick result, Smoking status, Serum Haemoglobin level, HDL cholesterol, LDL cholesterol - Use of the following drugs: ACE inhibitor, Statin, Diuretics, Opioids, Potassium-sparing diuretics |

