| List of Appendices Appendix 1 Inclusion exclusion flow chart for the diabetic cohort (CH1)  Appendix 2 Inclusion exclusion flow chart for the hypertension cohort (CH2)  Appendix 3 List of diabetic medication  Appendix 4 List of Read code for Essential Hypertension  Appendix 5 List of Read code for liver damage  Appendix 6 List of Read code of Anaemia  Appendix 7 List of BNF chapters for the HIV treatment  Appendix 8 List of BNF chapters for the malignancy treatment  Appendix 9 List of UGT1A1 inhibitors (list obtained from WHODrug Standardised Drug Groupings)  Appendix 10 List of covariates |

**Amendment -February 12^th^ 2021
E. Objectives, Specific Aims and Rationale,**

Objective for post-hoc analysis:

- To investigate the diabetic disease progression in relation to bilirubin levels in type2 diabetic patients.

| **Objective for post-hoc analysis**  4) To investigate the diabetic disease progression in relation to bilirubin levels in type2 diabetic patients, in a real-world setting. | **Outcome measure**  - Time to first introduction of additional anti-diabetic medication.  - Time to start of the insulin therapy | **Hypothesis tested**  4) Naturally elevated serum bilirubin level of type2 diabetic patients is associated with slower diabetic disease progression when measured by additional anti-diabetic medication therapy. |
| --- | --- | --- |

Rational:

In the analyses based on the original protocol, we found that high circulating bilirubin is associated with reduced renal diseases risk. We have based this analysis on two patient populations at risk of renal function decline, diabetes and hypertension. We have expected a much higher risk reduction for the diabetic patient cohort as bilirubin is known to increase insulin sensitivity, so the slower loss of glycemic control and bilirubin’s direct protective effect (through anti-oxidative effect) will reduce the kidney function decline. However, we did not find differences in risk reduction for both cohorts on the primary endpoint (eGFR decline, HR 0.88 for diabetic cohort and HR 0.91 for hypertensive cohort), while there was a larger risk reduction on the hypertensive cohort on the secondary endpoint (albuminuria, HR 0.89 for diabetic cohort and 0.82 for hypertensive cohort). This unexpected finding has made us required to directly evaluate bilirubin’s association with the key differences between these two cohorts (one cohort having normal glycemic control while the other has worse glycemic control)

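### Users of UGT1A1 inhibitors are excluded, but nothing visible handles users of drugs that induce the same enzyme, so some low bilirubin in the control group may be drug-induced

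*Protocol*

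**What the plan says.** The specific aims state each renal hypothesis for natural levels, for example "Naturally elevated serum bilirubin level of type2 diabetic patients is associated with slower degradation of the renal function". The Study Background says that bilirubin is "eliminated through glucuronidation by uridine diphosphate glucuronosyltransferase 1 family, polypeptide A1 (UGT1A1").

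The exclusion criteria in Definition of the Study population remove "Any user of UGT1a1 inhibitors (see Appendix 9) during the acute disease period". The drug list behind this is, by its title, "Appendix 9 List of UGT1A1 inhibitors (list obtained from WHODrug Standardised Drug Groupings"). No other appendix title mentions drugs acting on this enzyme.

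Selection of comparison group(s) or controls defines exposure over the same two years: "The serum bilirubin levels are determined by the average of all the available measurements during the acute disease period". Its grouping rule reads "We consider the patients with less than or equal to the median serum bilirubin level to be the control group"; everyone above the median is exposed.

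Under Exposures, Outcomes and Covariates, the drugs named for the Cox model are ACE inhibitors, statins, diuretics, opioids and potassium-sparing diuretics. The propensity score uses Appendix 10, which is not shown.

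**The concern.** By excluding inhibitor users, the protocol accepts that a drug acting on UGT1A1 makes measured bilirubin a poor guide to a person's natural level. The same reasoning applies in the other direction. A drug that increases UGT1A1 activity lowers measured bilirubin, and a patient with a naturally above-median level may then be counted as a control. The hazard ratio compares two groups, and the exclusion protects only one of them.

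No planned analysis that is visible would show this. The sensitivity analyses vary the weighting, the cut-off and the subgroup. The subgroups use the same five drug classes as the Cox model, so none isolates inducer users. Changing the cut-off, or treating bilirubin as continuous, still uses the drug-lowered value.

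At stake is whether the estimate refers to natural bilirubin, and whether patients who differ by the illness for which they take an inducer gather in the control group.

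**Working it through.** **Figures from the protocol.** Sample size considerations gives a planning hazard ratio of 0.8, 631 events, 0.047 events per person-year and over 300 000 person-years. The February 2021 amendment reports primary-endpoint hazard ratios of 0.88 (diabetes) and 0.91 (hypertension).

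The event count reproduces with the two-sided 5%, 80% power, 1:1 Schoenfeld formula: 4(1.960 + 0.842)² / (ln 0.8)² = 630.5, so 631. Then 631 / 0.047 = 13 426 person-years, stated as 13 500. The protocol states no figure on inducers, so the rest rests on assumptions.

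**Assumptions.** Inducers lower bilirubin by 0.3 on the log scale (exp(−0.3) = 0.74, about 26%). The between-person log SD is 0.4. A share *p* of 1% to 3% of the cohort uses inducers. The users' renal hazard is *r* = 1.3 to 2.0 times that of non-users.

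**Share of users in the low group.** Φ(0.3 / 0.4) = Φ(0.75) = 0.77.

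**Spurious hazard ratio with no bilirubin effect and no adjustment.** Each group is half the cohort, so users form 2*p* × 0.77 of controls and 2*p* × 0.23 of the exposed:

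HR = [1 + 2*p* × 0.23 × (*r* − 1)] / [1 + 2*p* × 0.77 × (*r* − 1)]

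| *p* | *r* | Calculation | HR | Share of ln 0.91 | Share of ln 0.88 |
|---|---|---|---|---|---|
| 1% | 1.3 | 1.00138 / 1.00462 | 0.997 | 3% | 3% |
| 2% | 1.5 | 1.0046 / 1.0154 | 0.989 | 11% | 8% |
| 3% | 2.0 | 1.0138 / 1.0462 | 0.969 | 33% | 25% |

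**Upper bound.** If every user falls in the control group, the null hazard ratio becomes 1 / [1 + 2*p*(*r* − 1)]. With *r* = 2 this is 0.980 at *p* = 1% and 0.909 at *p* = 5%.

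**Direction when bilirubin has a true effect.** Keep the worst case, let half the users be naturally above the median, and let their hazard follow their natural level. Relative to low-bilirubin non-users:

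- Control hazard = 1 − 2*p* + *p r*(1 + HR)
- Exposed hazard = HR + *p*(1 − HR)

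For a true HR of 0.80:

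| *p* | *r* = 1 | *r* = 1.5 | *r* = 2 |
|---|---|---|---|
| 1% | 0.804 | 0.796 | 0.789 |
| 5% | 0.818 | 0.783 | 0.750 |

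Setting the ratio of the two hazards equal to the true HR gives break-even at *r* = 1/HR, whatever *p* is. That is 1.25 for HR 0.80, 1.14 for 0.88 and 1.10 for 0.91. Below this value the bias is towards the null; above it, away from the null.

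**Against precision.** 300 000 × 0.047 = 14 100 events, so SE(ln HR) ≈ 2/√14 100 = 0.017. The three scenarios shift ln HR by 0.003, 0.011 and 0.031, or about 0.2, 0.6 and 1.9 standard errors. The event rate comes from a randomised trial; fewer events here would reduce these multiples. Power is not the issue, because a larger sample does not remove a systematic shift.

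**The case against.** The strongest defence is that the asymmetry has a rationale in the protocol. The hypotheses concern naturally *elevated* bilirubin, and removing drug-raised values is what keeps the exposed group true to that label. No hypothesis speaks of naturally low controls. The proposed mechanism is anti-oxidative, so it would act through the bilirubin actually circulating. On that view a patient with drug-lowered bilirubin really has low exposure and is not misclassified. This stands as a possible justification, but the protocol does not give it, and it does not answer the confounding by the illness being treated.

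The plan also has confounding control. Stabilised inverse probability weighting uses all the covariates in Appendix 10, which may include relevant drugs or comorbidities. The exclusions for HIV drugs, malignancy drugs, liver dysfunction, anaemia and alcohol dependence may already remove some users. The limitations section acknowledges unmeasured confounding. All of this stands, and the figures above, being unadjusted, probably overstate what remains.

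A reader might infer three stronger claims, none of which the documents support:

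- That the control group is in fact contaminated. No frequency of inducer use is given.
- That the error favours the hypothesis. This needs excess renal risk in users that remains after weighting, and the documents report none.
- That about a third of the observed effect could be spurious. That pairs the most extreme of the three scenarios with the weaker of the two reported hazard ratios.

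**Conclusion.** The drug exclusion is one-sided and unexplained, and nothing visible in the protocol deals with the other side. The control group may include patients whose low bilirubin is drug-induced; the documents do not show that it does so in numbers that matter.

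Under assumed use of 1% to 3% and a renal hazard ratio of 1.3 to 2.0 in users, the unadjusted spurious hazard ratio is 0.997 to 0.969, likely small against 0.88 and 0.91. The sign is not fixed: away from the null if users' renal risk is sufficiently raised, towards the null if it is not. The frequency of use, the size of the bilirubin shift, the spread of bilirubin and the renal risk are all assumptions. This is a cheap improvement and does not by itself call the main result into question.

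**What to change.** Build a list of UGT1A1 inducers from the same kind of source, and in the same way, as Appendix 9. Because the amendment shows that the main analyses have been run, the practical step is to repeat the primary analysis in both cohorts without patients who used a listed drug during the acute disease period. Report how many there were in each bilirubin group. The alternative is to add these users to the exclusion criteria. If neither is done, the protocol should say why only inhibitors are excluded and whether Appendix 10 contains covariates that capture inducer use.

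The cost is one drug list, one rerun and a loss of a few percent of patients at most. At 3% use, that is about 1 995 of 66 509 diabetic and 2 431 of 81 025 hypertensive patients in the primary analyses. The required 631 events would not be threatened.

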| Data/ Statistical Analysis Baseline characterization  The baseline characteristics will be described by the exposure groups (high and low bilirubin level at baseline). Summary statistics such as counts, average, standard deviation, median, and inter-quantile range will be tabulated.  Formal analysis of individual cohort  Multivariate Cox’s proportional hazard model with stabilized inverse probability weighting scheme (9,10) will be used to calculate the Hazard ratios (HR) with 95% confidence interval for the outcomes (worsening of eGFR, proteinuria, and albuminuria).  Sensitivity analysis  We will test the robustness of the results from the formal analysis by testing the sensitivity to   - the use of inverse probability weighting. (We will repeat the formal analysis without inverse probability weighting and compare the HR) - the cut-off value for the serum bilirubin level for dividing control and exposure group. (We will repeat the formal analysis with different bilirubin cut-offs and compare the HR) - the subpopulation of the patients. Subgroups will be made based on the following covariates: Age, Sex, smoking status, Baseline eGFR, Baseline UACR, Baseline protein dipstick result, Use of ACE inhibitor, Statin, Diuretics, Opioids, Potassium-sparing diuretics. (We will conduct subgroup analysis with test of interaction between the subgroup and exposure-control groups)   In addition, to investigate the possible bias introduced by the fact we are including only the patients with two or more bilirubin measurements at the baseline, we will repeat the above analyses but compare the patient population with baseline bilirubin measurement v.s. no baseline bilirubin measurements.  Additional analysis   - We will characterize bilirubin as continuous variable to understand the medically important nonlinear relationship between bilirubin concentration and outcomes. - We will build mixed effect model on eGFR and test statistical significance of bilirubin level as a covariate using likelihood ratio test to better understand the time course variation of eGFR in relation to bilirubin level. |
| Plan for addressing confounding We will use inverse-probability weighting to address the confounding. |
| Plans for addressing missing data We will use missing indicator method to handle missing data. |

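### One bilirubin median is fixed for routine results from many practices and about 12 years, and the named models carry no practice or index-year term, so the high group may partly reflect where and when patients were tested.

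*Protocol*

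**What the plan says.** **Exposure.** Under Selection of comparison group(s) or controls, the protocol states: "We will stratify the patients based on the population median of the patient mean baseline serum bilirubin levels from the tests table under ENTTYPE 158". Patients above the median are exposed; those at or below it are controls. The value for each patient is a mean over a window: "The serum bilirubin levels are determined by the average of all the available measurements during the acute disease period (2 years after the rolling index". At least two results are required. No standardisation by laboratory, practice or year is described, and the text does not say whether the median is taken per cohort or over both.

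**Source and period.** Under Definition of the Study population: "The study population will include patient records from January 2005 to January 2019". The index date is rolling, and the follow-up figure gives "Median follow up 5 years, minimum follow up 1 year". One of the events that end follow-up is "Either the date patient has transferred out from the practice", which shows that patients sit within practices. The number of practices or laboratories is not given.

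**Models.** The Cox covariates are "Age, Sex, Weight, BMI, Baseline eGFR, Baseline UACR, Baseline protein dipstick result, Smoking status, Serum Haemoglobin level, HDL cholesterol, LDL cholesterol", followed by five drug classes. For the weights: "We will use all the available covariates (see Appendix 10) to calculate the propensity score". Plan for addressing confounding names inverse probability weighting and nothing else.

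**Sensitivity analyses.** Under Data/ Statistical Analysis, one of them reads: "We will repeat the formal analysis with different bilirubin cut-offs and compare the HR". The others drop the weights, examine subgroups, and compare patients with and without baseline bilirubin. None is described as within practice or within period, and the Limitations section does not mention either.

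**The concern.** A common cut-off assumes that a given bilirubin value means the same in every practice and every year. If results read systematically higher in some practices or years, those contribute more exposed patients than controls, and the contrast becomes partly one between places and periods.

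Two features make this worth settling. First, every endpoint needs a recorded test: two consecutive low eGFR values, a positive dipstick, or a UACR above the threshold. How often a practice tests therefore affects when an event is recorded. Second, Study Background and Limitations both say that bilirubin varies with race, which is not among the named Cox covariates. If ethnic mix differs between practices (an inference, not a statement in the protocol), practice would carry information on bilirubin even with identical assays.

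The planned cohorts are so large that random error is small, so a modest systematic shift would not be hidden inside a wide interval.

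**Working it through.** **1. The plan's own figure.** Schoenfeld's formula with HR 0.8, two-sided 5%, 80% power and a 1:1 split: (1.960 + 0.842)² / (0.25 × (ln 0.8)²) = 630.5, so 631 events, as stated. Person-years: 631 / 0.047 = 13 426, stated as 13 500. The concern does not change these figures.

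**2. Precision at the planned size.** 300 000 person-years × 0.047 = 14 100 events per cohort. The standard error of the log HR is about 2/√14 100 = 0.017, so the 95% half-width is about 1.96 × 0.017 = 0.033. This ignores weighting and clustering.

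**3. Calendar span of the exposure.** With one pre-index year from January 2005, index dates start about January 2006. With a two-year acute period and at least one year of follow-up before January 2019, they end about January 2016. Bilirubin values then run from about January 2006 to January 2018, about 12 years.

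**4. Effect on who is called high.** Assume that a share f of the variance of patient-mean bilirubin (normal scale) comes from practice or period. A practice or period 1 SD above average has a share Φ(√f/√(1−f)) above the overall median. None of these f values is in the protocol.

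| Assumed f | High share at +1 SD / −1 SD | Misclassified, arccos(√(1−f))/π | True HR 0.80 seen as |
|---|---|---|---|
| 0 | 50% / 50% | 0% | 0.80 |
| 2% | 55.7% / 44.3% | 4.5% | 0.82 |
| 5% | 59.1% / 40.9% | 7.2% | 0.83 |
| 10% | 63.1% / 36.9% | 10.2% | 0.84 |
| 20% | 69.1% / 30.9% | 14.8% | 0.86 |

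The last column applies when place and period are unrelated to outcome. With misclassified share m it is (0.8(1−m) + m) / ((1−m) + 0.8m).

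**5. Effect when place is related to outcome.** After a median split of a normal exposure, the two groups differ in the mean practice component by √f × 2√(2/π) = 1.596√f, in SD units of that component. The shift in log HR is therefore ρ × SD × √f × 1.596, where SD is the between-practice SD of the log hazard and ρ its correlation with the practice bilirubin level. Assumed: SD 0.3-0.5 and |ρ| 0.2-0.4.

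| f | \|ρ\|, SD | Shift in log HR | Null seen as, ρ < 0 | Null seen as, ρ > 0 |
|---|---|---|---|---|
| 5% | 0.2, 0.3 | 0.021 | 0.98 | 1.02 |
| 5% | 0.4, 0.5 | 0.071 | 0.93 | 1.07 |
| 10% | 0.2, 0.3 | 0.030 | 0.97 | 1.03 |
| 10% | 0.4, 0.5 | 0.101 | 0.90 | 1.11 |

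Against the half-width of 0.033, these shifts run from about two thirds of it (0.021) to about three times it (0.101).

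**6. How large a correlation chance alone would give.** With K practices the chance correlation has a standard error of about 1/√K. For assumed K of 100 and 400 this is 0.10 and 0.05. At f = 10% and SD 0.3-0.5, a one-standard-error correlation moves a null HR to about 0.985-0.975 (K = 100) or 0.992-0.987 (K = 400), or as far above 1.

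**The case against.** The strongest reply is that the only stated confounding control is the propensity score, and its covariate list is not in the text at hand. That stands: a reader might infer that index year and practice are left out of the weights, but the protocol does not show it. What can be seen is limited. All area-level data options on the data request form are unticked and linked data are ruled out, so area deprivation measures are unlikely to be in the list, while index year, region or practice could be.

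Second, the protocol reports no variation in bilirubin between practices or over time. That also stands: the concern is a risk of unknown size, and at f = 0 it vanishes.

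Third, an offset unrelated to outcome only dilutes the HR, and step 6 shows that chance alignment over many practices gives small shifts. Correlations of 0.2-0.4 need a systematic reason. Testing habit is one candidate, but the protocol has no data on it, nor on the direction.

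Fourth, the primary event is a 30% fall from the patient's own baseline, so a stable proportional offset in eGFR cancels, and the Cox covariates capture part of the case mix. Both are fair, but neither deals with testing frequency, a change of assay during follow-up, or the bilirubin cut itself.

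Fifth, clustered standard errors are often left to an analysis plan, which may exist. Their absence here is not an error in itself. Limitations does concede unmeasured confounding, though in general terms only.

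**Conclusion.** The point holds as a design weakness of unknown size. The protocol fixes one cut on unstandardised multi-practice, multi-year results, and no model or sensitivity analysis in the visible text would show whether place or period contributes to the contrast.

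If place and period are unrelated to outcome, a true HR of 0.80 would be seen as about 0.82-0.86 for f of 2-20%. If they are related, a null effect would be seen as about 0.90-0.98 or 1.02-1.11 under the inputs of step 5. All those inputs are assumptions, and the sign is open.

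The February 2021 amendment reports primary HRs of 0.88 and 0.91, which are log HRs of −0.128 and −0.094. A reader might infer that practice or period differences explain them. The documents do not support that: the largest assumed shift (0.101) is smaller than the first and only just exceeds the second, it needs the most unfavourable corner of the range and the right sign, and dilution would work the other way. Nor should 14 years be read as the span of the exposure; that is the record span.

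**What to change.** - State whether Appendix 10 contains index year and practice or region, and whether the median is per cohort or pooled.
- Add calendar year of index to the Cox model, and to the propensity model if Appendix 10 lacks it.
- Report robust standard errors clustered by practice. These correct the intervals, not the bias.
- Add two sensitivity analyses: the weighted Cox model stratified by practice, and high versus low bilirubin defined against the median within practice and index-year band. The second also removes genuine differences in bilirubin between practices, so it belongs beside the main analysis, not in its place.

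No new data collection is needed, provided that the extract holds a practice identifier; the censoring rule implies one but the protocol does not say so. Intervals widen slightly, because a practice without events adds nothing to a stratified model, and small practices may need wider year bands. Primary analysis sets of 66 509 and 81 025 can absorb this. Since the amendment shows that the main results are known, the added analyses should be reported as post hoc.
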